### Sleep devices

#### Wahakura

The *wahakura* is a 36 × 72 cm flax bassinet, with no handles, and a 20 mm thick foam sponge mattress covered in a cotton pillowcase. They will be woven by a local weavers’ group, and supplied to the mother during the pregnancy, with some standard instructions as below.

#### Bassinet

A portable standing bassinet, custom designed in New Zealand for distribution to infants at high risk, will be used. This bassinet can easily be moved and transported in a car. The base will contain an identical 20 mm foam sponge mattress as used in the *wahakura*.

#### Safe sleep instructions

We recommend that babies always use the assigned sleeping device as their sleep place and, noting the portability of both devices, that the sleeping device is passed on to all carers (babysitter, grandparents, and extended family). *Wahakura* are to be used for every location where the baby sleeps. That is, it may be placed on the floor, on a mattress, on a flat couch, in a shared bed, or in a cot.

Babies should sleep on their back, with no pillows, face always clear of blankets, with no toys or loose objects in the sleeping environments. We recommend that direct bedsharing, that is bedsharing without a *wahakura or other protective device,* should be for cuddles and feeding only, and that the baby be put back into the *wahakura* or bassinet for sleeping.

Some options for safe bedding will be suggested for both the *wahakura* and the bassinet, for example, the sleeping sack (baby sleeping bag), or, as is usual for a bassinet, the blanket threaded under the mattress and wrapped over baby and then tucked in. Mothers will be routinely supplied with a Safe Sleep brochure outlining the above Safe Sleep messages.

### Outcome measures

Primary outcome measures for the infant will be derived from the overnight sleep study (amount of time head covered, amount of time in thermal comfort zone, number of hypoxic events and amount of time in the sleep device) and from surveys (full or exclusive breastfeeding at 3 and 6 months). Secondary outcomes identified from the sleep study include number of infant head covering events, number of parental (non-feed related) touching infant events, amount of time in the prone sleep position, the number of behavioural arousals, and the amount of time infant is awake overnight.

Psychosocial factors will also be measured. Using questionnaires, maternal environmental chaos will be measured at baseline. Social support, and social and economic stress will be measured at baseline and 3 months. Maternal depression and change in depression (from baseline) will be measured at 3 months and 6 months. Parenting factors, including beliefs about infant care, attachment, and parenting adaptation will be measured at baseline and 3 months using both the questionnaires and maternal salivary oxytocin levels at baseline, 1 month and 3 months. Maternal mind-mindedness will be measured at baseline, 3 and 6 months, using the questionnaires, and an audio recording of the mother talking about her baby (see Table 
1).

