### Bedsharing

Many case control studies have identified conditions in which bedsharing is associated with increased risk of sudden infant death. The most consistent finding is that exposure to cigarette smoke in utero greatly increases the risk of SIDS when bedsharing
[11, 12]. Other contributing factors include excessive maternal tiredness, infant overheating and household overcrowding
[12], the use of sedative drugs
[13], or alcohol
[14, 15] and maternal obesity
[16]. In the absence of any of these other factors, there is a suggestion that although bedsharing per se has some risk for babies under the age of 14 weeks
[15], the risk is significantly smaller than where there is smoking during pregnancy.

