### Temperature control

From our previous study
[49], we estimated that 32% of bedsharing babies and 3.5% of cot sleeping babies had a core-peripheral temperature difference of <1°C after they had been asleep for 3.5 hours, suggesting thermal stress from a warm environment. About 40 babies per group are needed detect a difference of this magnitude with 90% power using the 5% level of significance. Ideally, babies should be neither too hot nor too cold; 75% of the cot-sleeping babies were in the ideal comfort zone, where the peripheral temperature is between -1°C and -3°C of the core temperature. Two groups of 98 babies have the potential to detect a difference of 20% with 80% power using the 5% level of significance.

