### Measures

#### Sleep studies

A formal home sleep study will be completed when babies are 1 month old. After negotiation with the family, a researcher will visit the home in the evening, and set up the equipment for recording. We plan to use the minimum possible equipment, with the least possible attachments to the baby. Infrared video using a Swann wireless ADW-400 digital camera and recorder, and oximetry using a Massimo Rad 8 set to a 2 second averaging time (analysed using Visi-Download software) will be recorded. Four temperature probes will be used to measure infant toe and core temperature (measured over the liver) and room and outside temperature, using a flat film RTD temperature sensor (5×2 mm). Temperature will be recorded onto GP-HR general purpose 4 channel logger to be attached to the Massimo oximeter.

Video recordings will be viewed off-line using Noldus Observer XT, a software package for the collection, analysis, and presentation of observational data. The data will be coded according to a taxonomy adapted from that used in the Durham University Parent-Infant Sleep Lab (personal communication, [name], Parent-Infant Sleep Lab, Durham University; June 2012). Key categories will include infant sleep time, infant awake time, behavioural arousals, head covering events, breastfeeding events, infant sleep position, and maternal interactions. The software allows synchronisation with physiological recordings of oxygen saturation and temperature. Hypoxic events will be defined as decreases to <90% lasting >10 seconds. Infant peripheral temperature will be used as an indicator of thermal comfort. On the basis of our previous studies
[49] we decided to use a peripheral temperature of <34 degrees as indicating cold stress, or >36 degrees as indicating heat stress. The data will be analysed to identify behavioural events associated with hypoxic episodes or changes in infant temperature.

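### The only listed thermal outcome pools too hot with too cold, so a shift from cold to heat stress in the wahakura arm would be diluted, and fully hidden if the two changes are equal

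*Protocol article*

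**What the plan says.** The Outcome measures section of the protocol article gives "amount of time in thermal comfort zone" as a primary outcome from the overnight sleep study. No other primary or secondary outcome there is thermal, and the outcome list in the abstract agrees.

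The article describes thermal limits in two places, both two-sided:
- Temperature control (under sample size) puts the zone "where the peripheral temperature is between -1°C and -3°C of the core temperature", with the rationale "Ideally, babies should be neither too hot nor too cold".
- Sleep studies takes "a peripheral temperature of <34 degrees as indicating cold stress, or >36 degrees as indicating heat stress".

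Warm-side risk appears separately. The Bedsharing section includes "infant overheating and household overcrowding" among the contributors to risk when bedsharing. Temperature control reports from the group's earlier study that "32% of bedsharing babies and 3.5% of cot sleeping babies had a core-peripheral temperature difference of <1°C", interprets this as stress from warmth, and sizes that contrast at about 40 per group for 90% power. The same section says that "75% of the cot-sleeping babies were in the ideal comfort zone" and sizes a 20-point difference at 98 per group for 80% power.

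The first hypothesis under Overall study design is that the thermal environment does not differ significantly between the devices.

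**The concern.** A two-sided zone gives one number, time inside, from which the direction of any departure cannot be recovered. If one sleep place is warmer than the other, some babies move from cold into the zone while others move from the zone into heat. The first movement adds to time in the zone and the second takes from it, so the net change understates both.

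This matters because a null result is the favourable one under hypothesis 1, so an outcome that dilutes a rise in heat stress errs towards a finding of safety. The reverse misreading is also possible: a comfort-zone difference produced only by a change in cold time could be taken as evidence about overheating.

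**Working it through.** **Inputs**, all from the protocol article. Temperature control: comfort 75% in cot babies; warm 3.5% in cot and 32% in bedsharing babies; 98 per group for 20 points at 80% power; about 40 per group for the warm contrast at 90% power. Total numbers required: 100 per group with complete data at 1 month. The level is 5%, taken as two-sided.

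**1. The plan's own figures.** For 75% v 55%, the mean proportion is 0.65.

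n = [1.96·√(2·0.65·0.35) + 0.842·√(0.75·0.25 + 0.55·0.45)]² / 0.20² = 88.1, rounded up to 89.

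With continuity correction: n' = (88.1/4)·[1 + √(1 + 4/(88.1·0.20))]² = 97.8, rounded up to 98. This matches the stated 98. For 3.5% v 32% at 90% power the same formulas give 36 uncorrected and 43 corrected, which bracket the stated figure of about 40.

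**2. Implied cold share in cot babies.** 100 − 75 − 3.5 = 21.5%. This assumes that the warm and comfort figures describe the same babies at the same time and that the remainder are cold.

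**3. Power at 100 per group.** For proportions p1 and p2 with mean p:

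power = Φ[(|p1 − p2| − 1.96·√(p(1−p)·2/100)) / √((p1(1−p1) + p2(1−p2))/100)]

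- Comfort, 75% v 68%: (0.070 − 1.96·0.0638)/0.0637 = −0.87, power 19%.
- Heat, 3.5% v 15%: (0.115 − 1.96·0.0410)/0.0402 = 0.86, power 81%.

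Where comfort is 75% in both arms, the test rejects at its false-positive rate of 5%.

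| Wahakura warm | Wahakura cold | Comfort | Power, comfort zone | Power, heat |
|---|---|---|---|---|
| 15% | 10% | 75% | 5% | 81% |
| 25% | 0% | 75% | 5% | 99% |
| 25% | 10% | 65% | 34% | 99% |
| 25% | 21.5% (unchanged) | 53.5% | 89% | 99% |
| 32% | 0% | 68% | 19% | >99% |
| 32% | 10% | 58% | 72% | >99% |
| 32% | 21.5% (unchanged) | 46.5% | 99% | >99% |

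A simulation of the three-way split (40,000 runs, uncorrected chi-squared) agrees for comfort: 5% in the equal-offset cases and 19% at 32% warm with none cold. For heat it gives 84% at 15% warm, slightly above the formula.

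**4. The opposite case.** Suppose heat is unchanged and cold rises by 20 points, so that comfort falls from 75% to 55%. The comfort-zone test has 85% power, and a heat comparison stays at its false-positive rate of about 5%.

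**The case against.** The best defence is that the article plainly means to look at heat. It sizes a warm contrast, labels heat and cold stress separately, and names peripheral temperature among the safety analyses in the Contamination section; hypothesis 1 speaks of the thermal environment rather than of one summary. The outcome list may simply be condensed. This shows that the data and the intention exist. It does not make heat a listed outcome: the list is what the article fixes, and the other temperature analysis that Sleep studies describes, linking behaviour to temperature change, is not a comparison between arms.

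Two stronger readings are tempting, and the documents support neither.

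First, a reader might infer that the comfort zone would miss a rise in overheating outright. Full masking needs the fall in cold to equal the rise in heat. If cold stays at 21.5%, the comfort-zone test has 89% power at 25% warm and 99% at 32%. The 32% also comes from direct bedsharing, whereas the wahakura is a separate surface that the instructions allow on a floor, on a couch or in a cot. It is not a forecast for this device.

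Second, a reader might infer that only heat matters and that heat stress should replace the comfort zone. The article treats cold as undesirable too and sets a cold limit, and the device's thermal direction is unknown. Heat alone would be blind to harm from cold, as step 4 shows.

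Part of the stake, reading a non-significant result as safety, comes from the wording of hypothesis 1 and would affect any outcome. Pooling adds to that problem but is not its source.

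**Conclusion.** The point stands in a limited form. The one listed thermal outcome cannot separate heat from cold, although the article singles out the warm side as a bedsharing hazard. A trial run as written could therefore support hypothesis 1 while heat stress rises.

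How far the signal is lost depends on how much cold stress falls: not at all if cold is unchanged, completely if the changes are equal, and partly in between. At the earlier bedsharing rate of 32% warm, comfort-zone power lies anywhere from 19% to 99%, while a separate heat comparison stays above 99%.

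These figures illustrate the mechanism and do not estimate the trial's power. The 21.5% cold share is inferred: the article ties the warm figures to 3.5 hours of sleep and gives no time point for the 75%. The calculation uses proportions of babies, as the article's sizing does, while the listed outcome is an amount of time. The split under the absolute limits in Sleep studies is unknown. Pooling acts in the same direction on any of these scales.

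**What to change.** In Outcome measures, keep comfort-zone time. Add time in heat stress as its own prespecified thermal safety outcome, co-primary or key secondary, with time in cold stress beside it, both using the limits of whichever zone definition is kept. State that the comfort-zone result alone does not support the thermal part of hypothesis 1, and that the heat and cold comparisons must be reported with it.

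The same probes and recordings supply all three measures, so the cost is wording and a little analysis. There are two small downsides: one or two more comparisons, which need a place in the outcome hierarchy, and many zeros in heat-stress time, for which the planned t-test may suit poorly.

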**Table 1 Tab1:** **Outline of measures and when they will be performed**

	Age of child			
	Pregnancy	1 month	3 months	6 months
Maternal and family demographics^1^	X	-	-	-
Maternal smoking status	X	X	-	-
Maternal alcohol and recreational drug use^2^	X	X	-	-
Baby urinary cotinine		X		
Maternal salivary oxytocin and cotinine	X	X	X	-
Perinatal variables	-	X	-	-
Sleep study	-	X	-	-
Breastfeeding status	-	X	X	X
Dummy use	-	X	X	X
Frequency and duration bedsharing	-	X	X	X
Use of well-child/primary care and secondary care services	-	X	X	X
Environmental chaos^3^	X	-	-	-
Social support^4^	X	-	X	
Social and economic stress^5^	X	-	X	X
Maternal depression^6^	X	-	X	X
Beliefs about infant care^7^	X	-	X	-
Attachment and parenting adaptation^8^	X	-	X	-
Mind-mindedness^9^	X	-	X	X

^1^Family structure, maternal education, combined family income, ethnicity, type of accommodation, number of bedrooms.

^2^Derived from the Australian national drug strategy household survey
[42] and Australian health survey 2001
[43].

^3^Confusion, Hubub and Order Scale
[44].

^4^NSW Child Health Survey
[45].

^5^Measures used in POI.nz study (original source lost)
[46]. Economic stress as utilised by the Welsh Family & School Transition Project 2001 ([name], Personal Communication, June, 2007).

^6^Edinburgh Postnatal Depression Scale
[47].

^7^Questions designed by the authors to measure beliefs about infant care.

^8^Attachment and Adaptation Scales from the Parenting Stress Index
[48].

^9^Questions designed by the authors to measure mind-mindedness. We will also code a 5 minute audio recording of each mother talking freely about her baby.

### Sample size

Our previous studies comparing bed-sharing to cot-sleeping infants
[49, 50] have been used to determine sample size using two of our primary outcome measures. The third major outcome (breast-feeding proportion) is derived from national data on breast-feeding (full or exclusive) by ethnicity
[51].

### Head covering

The proportion of babies having an overnight sleep with a head covering episode by blankets was 1/37 and so, in order to detect a difference of 15% between babies sleeping in wahakura and cots with 80% power using the 5% level of significance, two groups of 88 babies would be needed.

Assuming the proportion of babies having an overnight sleep with a head-covering episode by blankets will be 3% when sleeping in a bassinette, 88 babies per group are required to detect a difference of 15% between babies sleeping in wahakura and cots with 80% power using the 5% level of significance.

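### The head-covering sample size of 88 per group does not follow from its stated inputs: a 15-point difference from 3% at 80% power needs 65 per group, or 78 with continuity correction

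*Protocol article*

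**What the plan says.** All places are in the Protocol article.

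- **Head covering** makes the same calculation in two consecutive paragraphs. The first takes its base from earlier work: "The proportion of babies having an overnight sleep with a head covering episode by blankets was 1/37", and concludes that "two groups of 88 babies would be needed". The second rounds the base: "Assuming the proportion of babies having an overnight sleep with a head-covering episode by blankets will be 3% when sleeping in a bassinette", and says "88 babies per group are required to detect a difference of 15% between babies sleeping in wahakura and cots with 80% power". Both cite a 15% difference "with 80% power using the 5% level of significance". Neither gives the assumed wahakura rate or says whether the test is one- or two-sided.
- **Temperature control** starts from 75% of cot-sleeping babies in the comfort zone and states: "Two groups of 98 babies have the potential to detect a difference of 20% with 80% power".
- **Breastfeeding** asks for 106 per group to move from 45% to 65%, and calls this a 20% increase. The plan's percentage differences are therefore absolute points.
- **Total numbers required** sets the target at 100 babies per group with complete data at 1 month, and 105 enrolled.

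**The concern.** Read as the Breastfeeding paragraph reads its own figure, a 15% difference from 3% means 3% v 18%. A gap that wide from so low a base needs well under 88 babies per group at 80% power. Either the difference, the number or the power is misstated, or the method differs from the one behind the neighbouring figures.

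What is at stake is interpretation. The first hypothesis under Overall study design is that the wahakura does not differ significantly from the bassinet on several measures, including head covering. A null result will be read against the difference that the trial could have detected. On the printed text a reader cannot tell whether that is 12 or 15 points, or at what power.

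**Working it through.** **Inputs.** Base 3%, or 1/37 = 2.7%. Difference 15 points. Power 80%. Level 5%. Equal groups. Sides are not stated; two-sided is assumed (z = 1.960 for the level, 0.8416 for 80% power).

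**Formulas.** With d = |p1 − p2| and p̄ = (p1 + p2)/2:

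- Uncorrected: n = [1.960·√(2p̄(1−p̄)) + 0.8416·√(p1(1−p1) + p2(1−p2))]² / d²
- Continuity-corrected: n_cc = (n/4)·[1 + √(1 + 4/(n·d))]²

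**Step 1. Which formula reproduces the plan's other figures?**

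| Comparison | Uncorrected | Corrected | Stated |
|---|---|---|---|
| Thermal comfort, 75% v 55% | 88.1 | 97.8 | 98 |
| Breastfeeding, 45% v 65% | 95.9 | 105.7 | 106 |

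Both reproduce only with the correction.

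**Step 2. Head covering as stated.** For 3% v 18%, p̄ = 0.105 and d = 0.15:

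- n = (0.8497 + 0.3538)² / 0.0225 = 64.4, so 65 per group
- n_cc = 77.1, so 78 per group

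From 1/37 (2.7% v 17.7%), n = 62.7 and n_cc = 75.5, so 63 and 76.

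**Step 3. Other variants of 3% v 18% at 80% power.**

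| Variant | Per group |
|---|---|
| Unpooled variance | 62 |
| Arcsine | 57 |
| Exact Fisher | about 71 |
| One-sided, uncorrected / corrected | 51 / 64 |
| 65 or 78 inflated for 5% dropout | 69 / 83 |

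None reaches 88. A relative 15% (3% to 3.45%) would need far more than 88.

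**Step 4. What 88 would give.** For 3% v 18% at 88 per group, power is 90.8% uncorrected and 85.8% corrected.

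**Step 5. What could give 88.**

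- 3% v 15% (12 points), uncorrected: (0.7932 + 0.3331)² / 0.0144 = 88.09. Power at 88 is 79.96%. Corrected, the same comparison gives 104.1, so 105.
- 75% v 55%, uncorrected: also 88.09. The match is exact because p̄(1−p̄)/d² is 5.6875 in both cases (0.09 × 0.91 / 0.0144 and 0.65 × 0.35 / 0.04), and the two formulas then agree.
- 3% v 18% at 90% power, uncorrected: 86, near but not equal.
- 1/37 v 15%, uncorrected: 83, so the 12-point explanation works only from the rounded 3%.

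**Step 6. Power at the planned 100 per group.**

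| Comparison | Uncorrected | Corrected |
|---|---|---|
| 3% v 18% (15 points) | 94% | 90% |
| 3% v 15% (12 points) | 85% | 78% |

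**The case against.** The strongest reply is that little follows from the error. The figure of 88 does not set enrolment: the target of 100 per group exceeds it and exceeds every number that a 15-point difference needs at 80% power. Taken at face value the error is conservative, because 88 gives more than the stated power for 15 points. This stands, and it limits the severity.

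A second reply concerns the origin. A reader might infer that the authors wrote a wahakura rate of 15% as a difference of 15%, and that the text should simply be changed to 3% v 15%. The documents do not support going that far. They give no wahakura rate. The 12-point reading fits only without the continuity correction that the thermal and breastfeeding figures need. An uncorrected thermal comparison gives the same 88, so a carried-over figure is also possible. The mismatch does not depend on which explanation is right.

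Three stronger readings also fail:

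- That this is the only size of harm the plan states. Temperature control gives others, including 32% v 3.5% for probable heat stress.
- That head covering is the lead safety outcome. Outcome measures lists several primary outcomes unranked, and its head-covering measure is time covered, whereas the calculation uses the proportion with any episode.
- That the 15 points would serve as a non-inferiority margin. The article sets no margin and plans no such test.

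**Conclusion.** The point holds as an arithmetic inconsistency, minor to moderate in weight. The stated base, difference, power and level lead to 63 to 65 per group uncorrected, or 76 to 78 corrected. The printed 88 is too large by 23 to 25, or by 10 to 12.

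The conclusion assumes a two-sided test and absolute points. The first is conventional, and a one-sided test would widen the gap; the second follows the plan's own usage under Breastfeeding. No standard variant tried recovers 88 at 80% power for a 15-point difference.

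The head-covering figure is also not shown to be on the same footing as its neighbours. If 12 points was intended, the corrected method would need 105 babies per group with data, slightly more than the planned 100. Whether that applies cannot be settled from the article.

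**What to change.** - Go back to the original calculation. State both assumed head-covering rates, the sidedness and the formula, then correct whichever of the difference, the number or the power is wrong.
- Use one formula for all outcomes. On the continuity-corrected basis, head covering needs 78 per group for 3% v 18%, or 105 for 3% v 15%.
- Give the power at the planned 100 per group on that same basis: about 90% for 15 points or 78% for 12 points (94% and 85% if all outcomes are put on the uncorrected formula).
- Merge the two paragraphs so that one base rate is used.

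The cost is wording and possibly a slightly less favourable stated power. Enrolment does not change.
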